### Patient and public involvement

Patients and the public have been actively engaged from the inception of this project and will continue to be engaged throughout the design, development, evaluation and dissemination, as outlined in this manuscript. Partnerships with consumer advocacy organisations (MHA and the Australia Self-Care Alliance) have helped identify the gaps in LBP service and will enable a collaborative approach to developing service solutions that address patient priorities. By using an iterative codesign process with ongoing feedback loops, this project aims to ensure the project development is aligned with the needs of all stakeholders, including patients, partner organisations, clinicians and the public. Partner organisations and participating consumers will contribute to the project evaluation, interpretation of results and dissemination of research findings.

### Participant recruitment and consent

#### Codesign consumer and clinician focus group participants

The codesign consumer group will be recruited through MHA’s consumer advisory committee and will include the research team’s consumer representative, as well as invited consumers from previous research projects. MHA’s consumer advisory committee and the research team will help identify and purposively recruit members to ensure representation across age groups and sex. The consumer group will include between 8 and 12 members.

The clinician group will include project members and invited clinicians recruited through professional networks of the research team. Recruitment will be purposive to ensure representation from both private and public sectors. The clinician group will include between 8 and 12 members. Eligible participants will be adult participants (≥18 years) who can communicate in English, have access to videoconferencing software (eg, zoom or Skype) and are available to attend an online meeting at a scheduled time and date. Invited participants will receive an electronic information sheet and provide consent electronically via an online REDCap (Research Electronic Data Capture) link, prior to participation. REDCap is a secure, web-based software platform designed to support data capture for research studies.^35^

#### Campaign awareness survey

Media campaign awareness will be assessed using a separate online panel survey administered by a commercial panel provider, with data that can be weighted to the regional population. The company will purposively recruit a sample of adults (≥18 years) residing in the Mid North Coast and residing in a comparison area, the Southern NSW Local Health District. A single campaign awareness question will be asked within existing panel surveys. This will allow us to determine campaign awareness in the exposed region and in a demographically similar region. Only aggregated, deidentified responses will be provided to the research team; therefore, individual informed consent is not required in accordance with institutional ethics approval.

#### Pre–post cohort study participants (from the helpline)

Two independent cohorts (prehelpline and posthelpline upgrade) will be recruited using consecutive sampling of helpline users presenting with a primary complaint of LBP. At the conclusion of their helpline call, helpline operators will verbally invite eligible users to participate in a research study evaluating the helpline service. Interested individuals will receive an electronic information sheet via an online (email or text) REDCap link. Eligible participants will be adults (≥18 years) who are able to provide informed consent for study participation and have sufficient understanding of written and spoken English to read and complete online forms, and have used the helpline service for advice/management of their LBP. Informed consent will be obtained electronically using REDCap’s e-signature feature, prior to research participation in accordance with the institutional ethics approval. Participants can only be enrolled once in the same research period (ie, in the preperiod or postperiod) but can participate in both. Consenting participants will receive an invitation to complete the baseline, 3-month and 6-month questionnaires via REDCap.

#### Cohort qualitative interviews

A purposive subsample of an estimated 15–20 (total) pre–post cohort participants will be invited to participate in individual qualitative interviews, to explore factors contributing to helpline uptake, user experience and contextual factors relevant to scalability. Sample size will be guided by data saturation and sampling approach designed to capture diverse perspectives across variables such as health confidence, helpline acceptability, age and LBP chronicity (completed as part of the participant-reported outcomes).

#### Stakeholder focus groups

Two stakeholder focus groups will be held as part of the process evaluation of the helpline: one with helpline operators and one with partnering health service providers (3–10 participants per group). Participants will be purposively selected to ensure a range of experiences are captured (eg, years of clinical experience, health profession). Eligible participants, adults (≥18 years), will be provided with the study information and consent forms electronically prior to attending an online meeting.

### Design

This project uses three overarching frameworks: (1) an iterative codesign that describes the implementation process,^33^ (2) the Practical Robust Implementation Sustainability Model (PRISM)^36^ used to evaluate and understand the contextual factors that influence implementation and effectiveness outcomes and (3) the Reach, Effectiveness, Adoption, Implementation and Maintenance (RE-AIM) framework^37^ to evaluate the project implementation and effectiveness.^38^
Figure 2 depicts the project flow chart incorporating these frameworks.

**Figure 2 F2:**
[figure not shown]
Project flow chart illustrating the iterative codesign and implementation process for the helpline infrastructure, media campaign and upgraded helpline service. Evaluation will be guided by the PRISM and RE-AIM frameworks. PRISM, Practical Robust Implementation Sustainability Model’ RE-AIM, Reach, Effectiveness, Adoption, Implementation and Maintenance.

#### Exploration

In this phase, project partner consultations with MHA’s organisational staff, helpline operators and their consumer advisory group will be conducted to understand current gaps in the helpline service and supporting systems, and potential barriers and facilitators to upgrading the service. Separate online group meetings will be conducted, one with available organisational staff (approximately 2–4 members) and one with the consumer advisory committee (approximately 5 members). These meetings will form part of existing partnership engagement agreements.

A review of MHA’s organisational needs, priorities and values will provide context for the design and suitability of the upgraded service in the design stages. This will be explored alongside a review of current helpline data, to provide a broader understanding of end-user needs and the resources and capacity of the helpline to meet those needs.

In addition, the research team and MHA, in consultation with a media agency, will identify suitable locations and strategies for the media campaign. This will consider the potential cost-effectiveness of advertising in each region, the available health services (eg, ED’s and urgent care clinics), and the representation of metropolitan, regional and rural locations.

#### Design and development

Codesign of the upgraded helpline service will be informed by focus groups conducted with two separate groups, one comprising consumers (potential helpline users) and the other comprising clinicians. The focus groups will be conducted separately to capture the distinct perspectives of each group. One online nominal group technique^39^ meeting (for each group) will be used to generate, discuss and prioritise the key components that should be included in the upgraded helpline design, addressing both consumer needs and clinician perspectives on what is appropriate and necessary to provide effective LBP management support. It is anticipated these meetings will take between 1.5 and 2 hours. The focus group findings will be incorporated into an initial design of the upgraded helpline, which will be presented to the research team, ensuring alignment with the project aims, MHA’s needs and a sustainable model of care as advocated by our partner organisations. This design will be refined through a feedback loop where focus group members will be invited to review the design via email and provide individual feedback, allowing further development.

The same focus groups and meeting structure will be used to codesign the targeted media campaign with the objective of raising awareness of the upgraded helpline service for LBP. Development of the media campaign will be guided by the key messages identified by consumers and clinicians to promote uptake of the upgraded service. Key campaign messages will be pilot tested with our research partners including MHA’s consumer advisory committee and refined before media content production. Key elements necessary for a successful media campaign (ie, consumer messaging, proportion of the target audience made aware of the campaign, target location and available resources, cost, long-term impact and sustainability) will be designed and developed in consultation with an externally contracted media agency.

The third component of the codesign phase will comprise the development of infrastructure needed to support the helpline. This will include the integration of software systems and resources to support the upgrade, and sustainable processes to monitor and evaluate the helpline. It will also involve outlining the roles and responsibilities of helpline operator staff to meet the increased demands of the upgraded helpline, employing new helpline staff and developing staff training to upskill operators in the delivery of the upgraded service and use of new systems. Fidelity checklists will be codesigned with helpline operators to evaluate delivery of the upgraded service and to identify changes needed to support ongoing delivery of the upgraded service.

### Testing and refinement

The upgraded helpline service and workflows will be tested through a two-step process: (1) A pilot phase with a small number of invited pilot users (non-public release). Pilot users will include members of our research partner organisations, project operations team and MHA’s consumer advisory group, ensuring representation from each partner. We anticipate a minimum of five users. Pilot users will complete the System Usability Scale^40^ to provide structured feedback on the usability of the helpline service. This process will be complemented by an online consultation with pilot users to explore the service functionality, ease of navigation and helpline operator communication. (2) Initial implementation trial and refinement 6 months prior to the media campaign. This will allow time to test the upgraded service in ‘real-world conditions’ prior to the media campaign and an anticipated increase in service users. It is estimated this will involve 50 participants based on MHA’s current monthly rate of LBP callers. These participants will be recruited consecutively following use of the helpline service (see the participant consent and recruitment section) and form the first 50 participants of the postupgrade cohort.

Cohort participants will rate their acceptability of the helpline service across several domains using a modified version of the Theoretical Framework of Acceptability Questionnaire (TFAQ).^41^ In addition, routine service information including the number of calls, call answer rates, peak call times, call duration, number of urgently referred cases, proportion of calls requiring follow-up and average follow-up calls will be collected in the initial implementation period (prior to the media campaign release).

This information will be combined to identify any operational, logistic or technical adaptations that need to be made prior to the full implementation stage.

### Implementation

Full implementation will encompass developments and adaptations of the upgraded service made during the testing-refinement phase. It will also involve the launch of the targeted media campaign. Importantly, this phase will incorporate findings from the project evaluation (outlined below) to further refine and develop the upgraded helpline service with respect to RE-AIM outcomes. The objective of this stage is to embed a process of ongoing evaluation that will support continued development and sustainability of the helpline service beyond the lifecycle of research funding.

### Media campaign

To increase reach, awareness, service use and potential impact of the upgraded helpline, a targeted mass media campaign will be conducted. Mass media campaigns use media sources such as radio, television and social media to disseminate information/messages to a large audience.^42^ Previous studies suggest that this method can effectively promote and increase calls to helpline services.^42^,^44^ The campaign messaging will be codesigned with consumers, the research team and a dedicated advertising agency to create a campaign strategy that aligns with the objectives of MHA’s helpline and the objectives of the partnership project. The media campaign content will be created in consultation with a professional content creation company and reviewed by the research team, partner organisations and consumers prior to launch.

### The tailored LBP component of the helpline service

The proposed model of care offered by the upgraded helpline will be centred around a ‘live telephone service’ providing an opportunity for individuals with LBP to share and discuss their LBP experience with a qualified healthcare professional. Importantly, the helpline will be a telephone and digitally based resource for people with LBP to help make sense of their pain, to provide information and advice to understand their management options and assist navigating the healthcare system and to support self-care. These core concepts align with patients’ perceived needs from a healthcare service for managing musculoskeletal pain,^45^,^48^ and the Australian Low Back Pain Clinical Care Standards.^13^ It is anticipated that the service will also include a screening and triage component to identify callers with suspected serious pathology. During triage, helpline operators will assess the urgency of symptoms and refer callers to the most appropriate healthcare provider such as the ED or general practitioner. In addition to triage for serious pathology, the helpline service will include ongoing assessment to identify callers who may not be suitable for helpline-based management alone. This may include individuals with multiple psychosocial impairments, poor mental health, progressing symptoms or minimal improvement in patient-reported outcomes. Where appropriate, helpline operators may assist in locating and/or facilitating contact with the local healthcare services to ensure timely and comprehensive management.

A detailed description of the codesign process, components included in the helpline upgrade, and the media campaign will be presented in a separate publication following the development and implementation of the upgraded helpline service.

### Evaluation

The RE-AIM framework^37^ will be used to evaluate the implementation and effectiveness of the upgraded helpline service. The framework includes five dimensions (RE-AIM) used to understand and evaluate the broader impact of the implementation and intervention across individual, setting and system levels (see table 1). PRISM^36^ will be used as an extension of the RE-AIM framework to guide the exploration of the contextual factors that influence the project outcomes. This includes the characteristics and perspectives of recipients (eg, helpline operators, stakeholders and users), the implementation and sustainability infrastructure (eg, helpline operator capacity vs caller demand), and external environment related to long-term sustainability and scalability of the helpline (eg, government funding and policies for primary care). It can also be used to understand and guide necessary adaptations to improve the intervention implementation process.^49^

**Table 1 T1:** Evaluation of implementation and effectiveness using the RE-AIM framework

Evaluation outcome	Study design	Data source	Time points	Outcome measure	Data analysis	Sample size
Reach						
Reach of the media campaign Reach of the helpline	Cross- sectional Interrupted time series	Population panel surveys Monthly helpline call numbers	(1) Pre–post media campaign (2) 18 months pre to 12 months postmedia campaign	Comparison of helpline awareness between two Local Health Districts LBP monthly call rates	χ² test for proportions Segmented regression	700 panel survey participants (post campaign) All LBP phone calls/services received
Effectiveness						
ED visits for LBP (population level) Self-reported healthcare service utilisation (individual level)	Interrupted time series Independent pre–post cohort design	All LBP ED visits recorded in the Local Health District targeted by the media campaign Pre/Post helpline cohort self-reported data.	18 months pre–post upgrade Baseline, 3 months for each cohort	Monthly LBP ED visits Self-reported healthcare service utilisation	Segmented regression Negative binomial regression for count of healthcare service utilisation	All adult ED LBP visits registered with corresponding health district database 295 cohort participants
Adoption						
Characteristics of helpline users (eg, different geographical regions and age groups)	(1) Mixed methods	Monthly helpline call numbers Cohort participant interviews	Continuous 18 months pre–post helpline upgrade Pre–post campaign period	LBP monthly call rates stratified by demographic Qualitative study using PRISM framework	Segmented regression with stratification Mixture of inductive and deductive thematic interview analysis	All LBP phone calls/services received 15–20 cohort participants
Implementation						
Fidelity of the upgrade helpline service to fidelity checklist Participants perceived acceptability of the helpline	(1) Process evaluation using mixed methods	(1) Data audit of provided services (2) Cohort self-reported data	Continuous data collection following the upgrade Pre–post cohort	Fidelity checklist TFAQ acceptability questionnaire	Implementation fidelity Descriptive (visual) analysis	20% random audit of all LBP services provided As per effectiveness outcome
Maintenance						
Sustainability of the upgraded helpline service	(1) Mixed methods	Purposive sample for qualitative study Monthly calls in post campaign period and individual effectiveness at 6 months.	Post campaign period for qualitative data (routine data will be continuous) Post campaign	Qualitative study using PRISM framework Proportion of calls post media campaign completion	Mixture of Inductive and deductive interview analysis Segmented regression and negative binomial regression for count of healthcare service utilisation	15–20 cohort participants, 3–10 participants per stakeholder group All LBP phone calls/services

ED, emergency department; LBP, low back pain; PRISM, Practical Robust Implementation Sustainability Model; RE-AIM, Reach, Effectiveness, Adoption, Implementation and Maintenance; TFAQ, Theoretical Framework of Acceptability Questionnaire.

#### Reach

Reach will be assessed to determine the extent to which the media campaign raises awareness of the helpline and influences service utilisation. This will be evaluated using two approaches:

(1) To evaluate media campaign reach, we will conduct population-based surveys in the ‘intervention’ region (the Mid North Coast Local Health District of NSW) targeted by the campaign, and a ‘control’ region (Southern NSW Local Health District) that will remain unexposed to the media campaign. The control region was chosen for its similarity in population size and distribution to the intervention region, as well as the geographical distance of approximately 450 km and different media markets, which are expected to minimise campaign crossover. Surveys will be administered online via a commercial panel company. The survey will include a single campaign awareness question assessing recognition of the helpline service along with basic aggregated demographic information (eg, age group, sex and postcode) to enable region comparisons. Surveys will be conducted at baseline (precampaign) and postcampaign to measure population awareness of the helpline. Sample size calculations are based on the postcampaign comparison between the two regions (baseline awareness will be summarised descriptively). Based on feasible sample sizes provided by the panel company, a total of 300 respondents in the intervention region and 400 in the control region will be surveyed at both time points. Assuming 0.05% of respondents are aware of the helpline in the control group, this provides 85% power to detect a 3% difference in awareness between regions at a two-sided significance level of 5%.

(2) To evaluate the impact of the campaign on service use, we will analyse the monthly call rates using retrospective data to compare the rates of unscheduled calls with a primary complaint of LBP. This will be analysed 18 months before and 12 months after the campaign begins. An interrupted time series design will be used to determine the effect of the media campaign on call volume.

#### Effectiveness (primary intervention outcome)

The effectiveness of the helpline service will be evaluated at both an individual participant and population (health district) level.

Participant-level effectiveness will be evaluated using a pre–post cohort study. The primary outcome to assess individual effectiveness will be self-reported healthcare use (eg, general practitioner and imaging usage). This will be compared between an independent cohort of participants with a primary complaint of LBP who use the original service, and an independent cohort who use the upgraded service. The primary outcome will be analysed 3 months post service initiation. Cohort participant questionnaires will also capture secondary outcomes including pain intensity,^50^ disability,^51^ quality of life,^52^ the validated single-item physical activity question,^53^ two-item pain self-efficacy,^54^ health confidence score^55^ and acceptability.^41^ Based on historical service volume data from the MHA helpline, we anticipate approximately 50 participants in the preupgrade period and will require a minimum of 208 participants in the postupgrade period to detect an event rate difference of 4 healthcare service utilisations between the preupgrade and postupgrade cohort, with 80% power and 5% type-1 error rate. This is the equivalent of a 40% difference based on an average health service utilisation rate of 10 services per participant over 12 months observed in unpublished work.^56^ Adjusting for a loss to follow-up of 15% in the postupgrade cohort, we will require 245 participants postupgrade to achieve the required 208 completers. Combined with the anticipated preupgrade cohort, the total sample size is 295 participants.

Population effectiveness will be evaluated using aggregated Local Health District data on ED presentations for patients with a complaint of LBP. The analyses will be restricted to the Mid North Coast Local Health District (or relevant hospitals) data corresponding with the location of the media campaign. An interrupted time series design will be used to analyse the monthly change in LBP presentation rates and any associated trend change following the introduction of the media campaign.

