A comparison of primary participant-reported outcome (self-reported healthcare service utilisation) and secondary outcomes, between the preupgraded and postupgraded helpline cohorts will be conducted. The primary outcome will be analysed at 3 months (as part of the effectiveness dimension) and 6 months (as part of the maintenance dimension). Healthcare service use will be collected as count data and analysed using negative binomial regression model. The rate ratio will be estimated comparing the postupgrade cohort to preupgrade cohort. Negative binomial regression will account for individual follow-up time and potential overdispersion due to non-independence of repeated measures. Matching with replacement will be used to address potential imbalances between cohorts in baseline demographics and to account for the anticipated smaller ‘unexposed’ preupgrade cohort compared with the larger ‘exposed’ postupgrade cohort. Sensitivity analyses will be conducted to assess the robustness of the findings.

Individual qualitative interviews will be conducted with purposively selected cohort participants to identify factors and processes that contributed to the helpline uptake, implementation and future scalability. These include acceptability and appropriateness (the extent to which the helpline is perceived as agreeable and relevant); advertising campaign effectiveness; individual factors (eg, participants’ socioeconomic status); and service outcomes (eg, the extent to which the helpline is perceived to be effective, patient centred, timely). Interviews will be semistructured, using a mixture of inductive and deductive thematic analysis drawing on the PRISM framework.^36^ An interview guide will be used to ensure the same topics are explored across individual interviews.

Focus groups with key stakeholder groups will be conducted online to identify factors and processes that contributed to helpline uptake, implementation and future scalability. The interview guide will be informed by findings from the implementation phase to align with observed barriers and enablers. Focus group data will be analysed using a combination of inductive and deductive approaches, drawing on the PRISM framework to guide interpretation.

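### The primary sample size is justified on a 12-month service count, but the primary outcome is healthcare use at 3 months, so the stated 80% power is not supported for the outcome tested

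*Protocol article*

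**What the plan says.** In the Protocol article, Effectiveness (primary intervention outcome), the cohort comparison is sized "to detect an event rate difference of 4 healthcare service utilisations between the preupgrade and postupgrade cohort", "with 80% power and 5% type-1 error rate". About 50 preupgrade participants are anticipated and at least 208 postupgrade are required. The difference is then put in relative terms, with its source, which is unpublished: "This is the equivalent of a 40% difference based on an average health service utilisation rate of 10 services per participant over 12 months". With 15% loss applied to the postupgrade cohort, 208 becomes 245, and the total is 295.

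The same section fixes the time of the primary outcome: "The primary outcome will be analysed 3 months post service initiation". Table 1 in the Evaluation section agrees ("Baseline, 3 months for each cohort"), and so does the Data analysis section, which places the 6-month analysis under maintenance. According to Participant-level data, cohort questionnaires are given at baseline, 3 months and 6 months only.

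The Data analysis section specifies negative binomial regression that allows for individual follow-up time and estimates a postupgrade-to-preupgrade rate ratio.

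**The concern.** The target difference and the mean behind it belong to a 12-month window. The outcome being tested belongs to a 3-month window, and no participant contributes 12 months of data. Nothing in the article converts one to the other.

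This matters in two ways. First, a difference of 4 services is presented as the target of the primary comparison, and a reader would take it as the effect the 3-month analysis can detect. Second, in a count model the precision of a rate ratio depends on the expected number of events per person. Cutting the window from 12 to 3 months cuts the expected events, so the same rate ratio is estimated less precisely from the same people. If the calculation used 12-month counts, the 80% belongs to an analysis that the trial will not perform, and an inconclusive 3-month result would be judged against too favourable a power claim.

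**Working it through.** **Inputs from the article:** 50 preupgrade and 208 postupgrade completers; 10 services per participant over 12 months; a 40% difference; 80% power; 5% type 1 error; negative binomial model with a rate ratio.

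**Assumptions, because the article does not give them:** the difference is a reduction (rate ratio 0.6); the test is two-sided; all 50 preupgrade participants are analysed, as the plan's own figure implies; the rate is constant over the year. Neither the dispersion k nor the exposure time used for 208 is stated.

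**1. The plan's visible arithmetic.** 208 / (1 − 0.15) = 244.7, rounded up to 245; 245 + 50 = 295. Both reproduce. The figure of 208 itself can be neither reproduced nor refuted without k and the exposure time.

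**2. The target on the 3-month scale.** 10 × 3/12 = 2.5 and 6 × 3/12 = 1.5, a difference of 1. A reduction of 4 from a mean of 2.5 is impossible.

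**3. Variance formula.** With expected counts mu1 (preupgrade) and mu2 (postupgrade):

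Var(log RR) = (1/mu1 + k)/50 + (1/mu2 + k)/208, and power = Φ(|ln 0.6| / SE − 1.96), where |ln 0.6| = 0.511.

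**4. If 208 came from 12-month counts (10 v 6).** Solving for 80% power gives k = 1.227. Check: (0.100 + 1.227)/50 + (0.167 + 1.227)/208 = 0.0265 + 0.0067 = 0.0332; SE = 0.182; 0.511/0.182 = 2.80; power 80%.

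Same people and same k at 3 months (2.5 v 1.5): (0.400 + 1.227)/50 + (0.667 + 1.227)/208 = 0.0325 + 0.0091 = 0.0416; SE = 0.204; 0.511/0.204 = 2.50; power 70.6%.

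- Two other choices of the variance under the null hypothesis (reference-group rate, pooled rate) give k = 1.236 and 1.203, with 3-month power of 71.5% and 68.5%.
- Fitting the negative binomial model to 1,500 simulated data sets at k = 1.22 gives 78% at 12 months and 68% at 3 months.
- The rate ratio detectable with 80% power at 3 months solves |ln RR| = 2.80 × SE(RR). At RR = 0.56, mu2 = 1.4, SE = 0.205 and 2.80 × 0.205 = 0.57, which returns exp(−0.57), about 0.56.

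**5. If 208 came from annual rates with a 0.25-year exposure.** Solving for 80% power at 2.5 v 1.5 gives k = 0.888 (0.79 to 0.93 across the three variance choices). Check: (0.400 + 0.888)/50 + (0.667 + 0.888)/208 = 0.0258 + 0.0075 = 0.0332, and power is 80% as stated.

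**6. Sensitivity to dispersion.** Power with 50 v 208 and a rate ratio of 0.6:

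| k | 12-month counts | 3-month counts |
|---|---|---|
| 0.25 | 100% | 97% |
| 0.5 | 99% | 91% |
| 1.0 | 87% | 77% |
| 1.25 | 79% | 70% |
| 1.5 | 72% | 64% |

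**7. Sensitivity to the constant-rate assumption.** If use is concentrated soon after the call, the 3-month mean is higher. With k = 1.227 and a rate ratio of 0.6, power is about 75% at a preupgrade 3-month mean of 4 and about 77% at a mean of 5.

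**The case against.** The strongest reply is that the analysis works on rates. A 40% difference is a rate ratio of 0.6 on any time base, the model allows for follow-up time, and the 4 can be read as an annual rate difference estimated from 3 months of data. On that reading nothing is impossible: the 4 merely lacks its time unit, and 208 may already rest on a 3-month exposure. The authors hold the true exposure time and dispersion, and the full protocol or analysis plan, not shown here, may give them.

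Much of this stands. A reader might infer that the 80% power is not delivered and that the cohort is underpowered. The article does not support that: 208 fits a 12-month exposure with k about 1.2 as well as a 3-month exposure with k about 0.8–0.9, and in the second case 80% holds. Nor is there an arithmetic slip, since 245 and 295 reproduce. The 2.5 v 1.5 means rest on a constant rate, and k may differ between a 3-month and a 12-month window.

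What remains is more than a detail left to another document. The article publishes a target, a mean and a power for the primary comparison, and ties them to a window that differs from the outcome window in the same section. Even on the favourable reading, the difference of 4 misdescribes the 3-month comparison unless it is labelled an annual rate.

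**Conclusion.** The point holds in conditional form. The target difference and reference mean are on a 12-month base, the primary outcome is on a 3-month base, and nothing bridges them. The stated 80% power is therefore not supported for the outcome tested, which is not the same as shown to be wrong.

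The size depends on what was done. If 12-month counts were used, with a constant rate and equal dispersion in the two windows, the loss is roughly 10 percentage points, and the effect detectable with 80% power moves from a 40% to about a 44% reduction. If a 3-month exposure was used, there is no loss and only the wording is at fault. The correction is still needed in either case, because it concerns the justification for the primary effectiveness comparison.

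**What to change.** Rewrite the sample-size paragraph on the 3-month scale:

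- give the expected 3-month means in each cohort and say whether a constant rate was assumed;
- state the target as a rate ratio of 0.6;
- state the exposure time and dispersion used to obtain 208;
- replace the difference of 4 as the primary target, or label it explicitly as an annual rate;
- recompute and report the power, or the rate ratio detectable with 80% power, that 50 v 208 gives at 3 months.

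The authors should use their own dispersion and recomputed power. The 70% above is a reconstruction under stated assumptions and should not be copied in. No extra participants and no change of design are required. The cost is a short rewording and a possibly less favourable stated power.
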